## Abstract

**Introduction:**

The role of commensal microbiota in systemic diseases, including brain diseases, has attracted increasing attention. Oral infectious diseases, such as dental caries and periodontitis, are also involved in cerebrovascular diseases and cognitive impairment. Cerebral microbleeds (CMBs) and intracerebral hemorrhage due to small vessel disease (SVD), are presumably associated with a high risk of vascular cognitive impairment and stroke. We previously reported that *Streptococcus mutans* (*S. mutans*, the main pathogen of dental caries), harboring the *cnm* gene that encodes the collagen-binding protein Cnm, is associated with the development of hypertensive intracerebral hemorrhage and aggravation of CMBs. We also proposed a mechanism by which the circulating Cnm-expressing *S. mutans* causes intracerebral hemorrhage or CMBs; it binds to denuded basement membranes mainly composed of collagen IV through damaged tight junctions or it directly invades endothelial cells, resulting in blood-brain barrier injury. In November 2018, we initiated a multicenter, prospective cohort study (RAMESSES: Risk Assessment of Cnm-positive *S. mutans* in Stroke Survivors; UMIN Clinical Trials Registry: UMIN000045559) to explore the longitudinal association between Cnm-positive *S. mutans* and CMBs with comprehensive dental findings, which should determine the effect of Cnm-positive *S. mutans* in the oral cavity on the risk of CMB development and cognitive decline.

**Methods:**

Fifteen domestic institutes will be enlisted to enroll 230 patients who have at least one CMB in the deep brain area and develop a stroke within the past year. The prevalence of Cnm-positive *S. mutans* based on oral specimens and dental hygiene will be examined. The primary outcome is the number of newly developed deep CMBs. The secondary outcomes include the new development of lobar, subtentorial, or any type of CMBs; symptomatic intracerebral hemorrhage or ischemic stroke; changes in cognitive function or frailty; major bleeding; all-cause mortality; and antibody titers against periodontal pathogens. The observation period will be 2 years.

**Discussion:**

The 2-year longitudinal prospective cohort study is expected to establish the role of Cnm-positive *S. mutans* in SVD including CMBs and intracerebral hemorrhage from the perspective of the “brain-oral axis” and provide guidance for novel prophylactic strategies against Cnm-positive *S. mutans*-induced SVD.

## Introduction

Small vessel disease (SVD) refers to a variety of pathological, clinical, and neuroimaging changes that are caused by damage to the perforating cerebral arterioles, capillaries, and venules. Vascular pathologies underlying SVD include lipohyalinosis, fibrinoid necrosis, microatheroma, microaneurysms, and segmental arterial disorganization (1, 2). White matter hyperintensities (WMHs), lacunes, perivascular spaces, and cerebral microbleeds (CMBs) detected by brain magnetic resonance imaging (MRI) are major neuroimaging markers of SVD (3, 4). Among them, CMBs appear as small circular or elliptical lesions with a size of 10 mm or less that have a low signal intensity on gradient-echo T2^*^-weighted images (T2^*^WI) obtained by brain MRI (5–7). In addition, CMBs are an independent risk factor for cognitive impairment (8) and stroke (9), especially intracerebral hemorrhage (ICH) (10). It is well-known that the vascular risk factors, including hypertension, diabetes, dyslipidemia, and smoking, play important roles in developing and exacerbating SVD mediated by oxidative stress and vascular inflammation resulting in endothelial damage and disruption of the blood-brain barrier (BBB) (1). However, the effect of vascular risk factors on WMHs may be limited because WMHs have a substantial “non-vascular” or non-atheromatous etiology (4). This notion may be supported by the fact that the modification of vascular risk factors is not sufficient for the prevention and treatment of SVD.

Numerous studies have found an association between human microbiota and many pathological conditions, including cardiovascular diseases, diabetes, obesity, rheumatoid arthritis, Alzheimer's disease, and multiple sclerosis, which lead to the elucidation of the molecular mechanisms underlying this association (11). Specifically, the relationship between oral infections and cardiovascular diseases has been examined in several observational studies (12) and interventional studies (13). However, it remains to be fully elucidated which oral bacteria among more than 700 species are involved and how these causative agents exert the deleterious effects that induce systemic pathological changes (14). *Streptococcus mutans* (*S. mutans*) is a gram-positive bacterium and a major pathogen responsible for dental caries (15). Cnm, encoded by the *cnm* gene, is a cell-surface 120-kDa collagen-binding protein of *S. mutans* (16). Intravenous administration of Cnm-expressing *S. mutans* (Cnm-positive *S. mutans*) aggravates ICH in stroke-prone spontaneously hypertensive rats and cerebrovascular-endothelial-injured mice (17). We also reported that oral carriage of Cnm-positive *S. mutans* is associated with the prevalence of deep (basal ganglia and thalamus) CMBs and ICH (odds ratio: 4.5 vs. ischemic stroke) (18), and it is linked to an increased deep CMB incidence (incidence rate ratio: 13.9), based on cross-sectional studies (19), and to the severity of deep CMBs according to a longitudinal retrospective study (20). Cnm-positive *S. mutans* is also associated with cognitive impairment, accompanied by increased CMBs (19, 21).

Thus, cross-sectional and retrospective studies have identified strong associations of Cnm-positive *S. mutans* with ICH, deep CMBs, and cognitive dysfunction. However, the long-term effects of Cnm-positive *S. mutans* on SVD remain to be elucidated. In addition, the relationship between Cnm-positive *S. mutans* and oral hygiene and periodontal disease remains unknown. Therefore, in November 2018, we initiated a multicenter, prospective cohort study named RAMESSES (Risk Assessment of cnM-positivE S. mutans in StrokE
Survivors) to explore the longitudinal association between Cnm-positive *S. mutans* and SVD, including CMBs, with comprehensive dental findings. In this article, we detail the protocol for the RAMESSES study (Figure 1).

**Figure 1 F1:**
[figure not shown]
Research protocol of the RAMESSES study. The RAMESSES study is a multicenter, prospective, longitudinal, observational study to investigate the role of Cnm-positive *Streptococcus mutans* in the development of SVD and vascular cognitive impairment. Fifteen Japanese institutes participate in this study using a standardized MRI protocol. TIA, transient ischemic attack; CMBs, cerebral microbleeds; mRS, modified Rankin Scale; ICH, intracerebral hemorrhage; IS, ischemic stroke; MRI, magnetic resonance imaging; MoCA, Montreal Cognitive Assessment; CDR, clinical dementia rating.

## Methods

### Study Design and Setting

The RAMESSES study is a multicenter longitudinal prospective cohort study. The purpose of the study is to investigate the relationship between Cnm-positive *S. mutans* and SVD. The study will involve 15 institutes, including the National Cerebral and Cardiovascular Center (NCVC) as the central coordinating center located in Japan. The study will register 230 patients who develop stroke within 1 year after onset and are diagnosed with at least one hemorrhagic lesion involving CMBs or ICH in the deep area detected on T2^*^WI. The primary and secondary outcomes will be assessed at baseline, 6, 12, 18, and 24 months after written informed consent is obtained. We will conduct the assessments according to Table 1 for 2 years. The study protocol has been approved by the Research Ethics Committee of each participating center (NCVC protocol number: M29-133), and this study has been registered with the University Hospital Medical Information Network (UMIN) Clinical Trials Registry (UMIN-CTR: UMIN000045559). Each participant will be provided a detailed explanation of the purpose and potential risks of the study, and written informed consent will be obtained.

**Table 1 T1:** Study schedule.

	**Baseline**	**Follow-up visits**			
		**6 months**	**1 year**	**1.5 years**	**2 years**
Patient characteristics	X				
Physical examinations	X	X	X	X	X
Brain MRI	X		X		X
MoCA	X		X		X
CDR	X				X
GDS	X				
Clinical Frailty Scale	X				X
Laboratory tests	X				
Dental examinations	X				
Assessment of *cnm*	X				
Serum antibody titers against periodontal pathogens	X				

*MRI, magnetic resonance imaging; MoCA, Montreal Cognitive Assessment; CDR, Clinical Dementia Rating; GDS, Geriatric Depression Scale. The mark ‘X' means conduction of assessments*.

### Eligibility Criteria

Inclusion criteria are defined as follows: (1) patients with stroke (cerebral infarction, ICH, or subarachnoid hemorrhage) or transient ischemic attack that developed within the past 365 days; (2) patients over 40 years of age; (3) patients whose modified Rankin Scale (mRS) score is 4 or less; (4) patients who have deep ICH or at least one deep CMB on T2^*^WI performed within the past 365 days; and (5) written informed consent has been obtained from the patients themselves or the proxies. Exclusion criteria are as follows: (1) patients who are contraindicated for MRI examination because of the presence of some metallic implants, such as pacemaker devices; (2) patients with bleeding diathesis; (3) patients who participate in other intervention trials; (4) patients who cannot conduct the Montreal Cognitive Assessment (MoCA) due to severe dementia, deafness, or visual impairment; (5) patients who have no remaining teeth; or (6) patients whose participation is judged as inappropriate by the principal investigator or sub-investigators if a patient is not deemed to have capacity to provide fully informed consent or is too unwell at the time of recruitment (Table 2).

**Table 2 T2:** Eligibility criteria.

**Inclusion criteria**
**Patients must:**
• have been diagnosed with a stroke within the past year
• be ≥40 years of age when providing written informed consent
• have a modified Rankin Scale score in the range of 0–4
• have at least one deep CMB or deep ICH
**Exclusion criteria**
**Patients are ineligible if they:**
• are contraindicated to brain MRI
• have bleeding diathesis
• cannot take MoCA because of severe dementia, auditory disturbance, or visual impairment
• have no teeth

### MRI Evaluation

All 3.0 Tesla MRI examinations will be performed using the following standardized MR imaging protocol. All slices will be taken parallel to the orbitomeatal line from the base of the skull to the vault. The imaging protocol includes T2^*^WI, fluid-attenuated inversion recovery (FLAIR), diffusion-weighted imaging (DWI), and apparent diffusion coefficient. The sequence parameters of T2^*^WI are as follows: voxel size, 0.7 × 0.7 × 4.0 mm; slice gap, 0 mm; flip angle, 20°; field of view, 230 mm; echo time, 12 ms; repetition time, 686 ms. The sequence parameters of FLAIR are as follows: voxel size, 0.7 × 0.7 × 5.0 mm; slice gap, 1 mm; flip angle, 150°; field of view, 230 mm; echo time, 114–117 ms; repetition time, 12,000 ms. The sequence parameters of DWI are not restricted. CMBs and symptomatic ICH will be evaluated using T2^*^WI-MRI. CMBs in deep or lobar areas indicated below will be defined and counted according to the Brain Observer MicroBleed Scale (5) or the Microbleed Anatomical Rating Scale (22). CMBs will be categorized into three groups: (1) deep CMBs defined elsewhere (5, 22), (2) lobar CMBs in the cortical gray or subcortical white matter, and (3) subtentorial CMBs in the cerebellum or brain stem. CMBs in any brain region (any CMB) will also be recorded. Newly developed CMBs will be recorded at follow-up after 1 and 2 years. Symptomatic ischemic stroke (IS) will be evaluated by DWI. Lacunes and WMHs will be evaluated using FLAIR images. A lacune is defined as a supratentorial hypointense lesion 3–15 mm in diameter with a hyperintense rim. Periventricular hyperintensities (PVHs) and deep white matter hyperintensities (DWMHs) will be scored using the Fazekas scale (23).

### Outcomes

The primary outcome is the number of newly developed deep CMBs. The secondary outcomes include (1) new development of lobar, subtentorial, or any type of CMBs; (2) development of symptomatic ICH or IS; (3) change in cognitive function assessed by MoCA and clinical dementia rating (CDR), and in frailty according to the Clinical Frailty Scale version 2.0 (24); (4) major bleeding defined by the International Society on Thrombosis and Hemostasis criteria; (5) all-cause mortality; and (6) serum antibody titers against periodontal pathogens.

### Sample Size Estimates

The sample size was determined by feasibility, but it was ensured to be substantial enough to perform the primary analysis. According to recent studies, the general prevalence rate of Cnm-positive *S. mutans* is 7–20% (19, 25–27). Our previous retrospective study revealed that patients with Cnm-positive *S. mutans* has an incidence rate ratio (IRR) of 13.9 (4.3–44.5) when compared with patients without (20). In this study, the minimum number is 223 subjects (27 subjects with Cnm-positive *S. mutans* and 196 without) based on Cnm-positive *S. mutans* prevalence of 12%, IRR of 4.3 (equivalent to the lower limit of the 95% confidence interval), a significance level of 5%, 90% power, and a follow-up period of 2 years. Therefore, we will recruit 230 subjects with considering a dropout rate of 10%.

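### Recruiting 230 does not allow for 10% dropout on a stated minimum of 223: it leaves 207, so the 90% power claim does not hold as written

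*Protocol article*

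**What the plan says.** The Sample Size Estimates section of the protocol article states that "the minimum number is 223 subjects (27 subjects with Cnm-positive *S. mutans* and 196 without"). Its inputs are:

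- exposure: "based on Cnm-positive *S. mutans* prevalence of 12" per cent;
- effect: "IRR of 4.3 (equivalent to the lower limit of the 95% confidence interval");
- error rates and duration: "a significance level of 5%, 90% power, and a follow-up period of 2 years".

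The next sentence draws the recruitment target from this: "Therefore, we will recruit 230 subjects with considering a dropout rate of 10" per cent. The abstract repeats the target ("Fifteen domestic institutes will be enlisted to enroll 230 patients"), as does Study Design and Setting.

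The section opens by saying that feasibility fixed the size, while assuring the reader that it is large enough for the primary analysis.

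On the source of the effect size, the section credits the ratio of 13.9 (4.3–44.5) to the group's retrospective study, reference 20. The Introduction gives the same figure as "incidence rate ratio: 13.9), based on cross-sectional studies (19") and cites reference 20 separately, for a longitudinal retrospective finding on severity of deep microbleeds.

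**The concern.** If 223 is the minimum for 90% power and 10% of patients are expected to be lost, recruitment must exceed 223 by enough that 223 remain. An excess of 7 looks too small for that. The minimum, the dropout rate and the target cannot all be right.

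Readers will use the stated power to interpret a null primary result. If the stated dropout occurs, the study is no longer a 90%-powered one on its own figures. The primary comparison also rests on a small exposed group, which would fall from 27 to about 25.

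The attribution of 13.9 matters because its lower limit, 4.3, is the planning effect. The primary outcome counts newly developed deep microbleeds, and a cross-sectional study does not observe lesions arising over time. Whether the planning ratio describes new or existing lesions therefore depends on which study supplied it.

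**Working it through.** **Inputs, all from Sample Size Estimates:** minimum N = 223 (27 Cnm-positive, 196 negative); prevalence 12%; IRR 4.3; significance level 5%; power 90%; 2 years; dropout 10%; target 230. The section does not give a baseline microbleed rate, a dispersion or the sidedness of the test.

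**Step 1. The split reproduces.** 0.12 × 223 = 26.8, rounded to 27, and 27 + 196 = 223.

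**Step 2. The dropout step does not reproduce.**

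| Calculation | Result |
|---|---|
| Usual inflation, N/(1 − d) = 223/0.90 | 247.8, so 248 |
| Cruder inflation, N × (1 + d) = 223 × 1.10 | 245.3, so 246 |
| Left after 10% loss, 230 × 0.90 | 207 |
| Shortfall in evaluable patients, 223 − 207 | 16 |
| Shortfall in recruits, 248 − 230 | 18 |
| Loss that 230 can absorb, (230 − 223)/230 | 3.0% |
| Cnm-positive patients left, 0.12 × 207 | 24.8, about 25 |

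Neither convention gives 230. The target would fit a minimum of 207, since 207/0.90 = 230, but the section states 223. If 223 already included dropout, the evaluable number would be 223 × 0.90 = 200.7, about 201. Then 223 would not be the minimum and the text would still be inconsistent.

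**Step 3. Consequence for power.** With no baseline rate, 223 cannot be derived independently. I take it to give exactly 90% power and solve for the control mean μ₀ that this implies, using a two-sided Wald test of the log rate ratio with Poisson variance:

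- Implied standard error: ln(4.3)/(1.960 + 1.282) = 1.4586/3.2415 = 0.450.
- Variance: (1/μ₀) × [1/(27 × 4.3) + 1/196] = 0.01372/μ₀. Setting this equal to 0.450² = 0.2025 gives μ₀ = 0.068 new deep microbleeds per control patient over 2 years.
- Power = Φ(ln 4.3/SE − 1.960), with exactly 12% exposed:

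| Evaluable N | SE | ln 4.3/SE | Power |
|---|---|---|---|
| 207 | 0.468 | 3.115 | 87.6% |
| 223 | 0.451 | 3.233 | 89.9% |
| 230 (no dropout) | 0.444 | 3.284 | 90.7% |

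The row for 223 shows 89.9% because 12% of 223 is 26.76 rather than 27.

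**Step 4. Sensitivity to the formula.** Each variant was re-solved to give 90% at 27/196 and then evaluated at 25/182: two-sided Wald 87.7%, one-sided Wald 88.0%, square-root transform 87.7%, score-type with pooled null variance 88.3%. The loss is about 2 points throughout.

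**Step 5. Partial follow-up.** New microbleeds are recorded at 1 and 2 years. Assume that the 23 dropouts contribute half their person-time on average. The effective number is then 207 + 11.5 = 218.5, and power is Φ(3.2415 × √(218.5/223) − 1.960) = Φ(1.249), about 89.4%. That is still below 90%.

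**The case against.** The strongest reply is that this is a small slip in a study whose size was set by feasibility. The power loss is about 2 points at most, and less with partial follow-up. By the same back-calculation, 207 patients reach 90% power at an IRR of about 4.48 instead of 4.3, and 4.3 is already the lower confidence limit of an estimate of 13.9. Prevalence matters far more: over the section's own range of 7–20%, power at 223 runs from about 77% to 95%. The power figures are also conditional, because the rate, dispersion and sidedness are not stated and the primary model is quasi-Poisson. Finally, the citation point is separate from the dropout arithmetic, and a ratio from a count model can carry the label IRR in cross-sectional data.

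Much of this stands as a limit on the size of the problem, and the power figures should carry their assumption. None of it reconciles the numbers. Feasibility may justify stopping at 230, but the section still presents 230 as following from 223 and as allowing for 10% loss. Partial follow-up softens the loss without turning a 3% margin into a 10% one. On the citation, the document cannot show which reference is right, only that its two sections disagree.

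**Conclusion.** The concern holds. On the document's own figures, 230 recruits with 10% dropout leave 207 evaluable patients against a stated minimum of 223. The target covers about 3% loss. This part is plain arithmetic and rests on no assumption.

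The cost in power is modest: about 88% instead of 90% if dropouts contribute nothing, and between those values if they contribute partly. These figures assume that 223 gives exactly 90% power and that the variance scales with N as in the formulas above. They do not verify 223 itself. The implied control mean of 0.068 further assumes Poisson dispersion and a two-sided Wald test.

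It should be corrected because it is a wrong figure in the justification for the primary outcome. The conflicting attribution of 13.9 is a secondary point that needs reconciling.

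**What to change.** Rewrite the last sentence of Sample Size Estimates in one of these ways:

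- **Keep 230 and 10% dropout:** state that about 207 patients (about 25 Cnm-positive) are expected to be evaluable, giving about 88% power at an IRR of 4.3. Say that this is scaled from 90% at 223, or recompute it with the baseline rate used in the original calculation.
- **Keep 230 and 90% power:** state that the target allows for about 3% dropout.
- **Keep 90% power and 10% dropout:** raise the target to 248, here and wherever 230 appears.

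In the same edit, check which study supplied the IRR of 13.9 (4.3–44.5), and make the Introduction and Sample Size Estimates agree on the reference and the study design.

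The first two options cost one sentence and a slightly less favourable statement, with no extra patients. The third costs 18 more recruits.

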### Dental Examination and the Evaluation of Cnm-Positive *S. mutans*

Dental examinations will be conducted by well-trained dentists at each institute. Dental examinations will include (1) checking for the presence of dental caries; (2) dental radiography; (3) probing pocket depth assessed from the free gingival margin to the bottom of the sulcus or pocket; (4) full-mouth bleeding score, which is defined as the number of sites with gingival bleeding on probing divided by the total number of sites per mouth and multiplied by 100 (28); (5) the number of remaining and deficit teeth excluding the third molars; (6) the decayed, missing, and filled teeth (DMFT) index as an indicator of dental history or health (29). Sample collection and detection of Cnm-positive *S. mutans* will be performed using the following standardized protocol: oral saliva and dental plaque specimens will be collected from the patients using Seed-swab Type ⋎3 (Eiken Chemical, Tokyo, Japan). These samples will be inoculated on Mitis-Salivarius medium with bacitracin (MSB, 100 U/ml; Sigma-Aldrich, St. Louis, MO, USA) and 15% sucrose (MSB agar) and anaerobically incubated at 37°C for 48 h. The *S. mutans* colonies will be isolated and cultured in Brain Heart Infusion Broth (Difco Laboratories, Detroit, MI, USA) at 37°C for 24 h. Then, DNA from each strain will be extracted and analyzed by polymerase chain reaction using species-specific MKD primers to identify *S. mutans* isolates (27) and *cnm* primers to detect the *cnm* gene (16). A collagen-binding assay with type I collagen will be conducted to examine the collagen-binding activity of each isolated *S. mutans* strain, according to the method described elsewhere (30), with some modifications (27). The activity tests will be performed under fixed conditions using 1 mg of type I collagen and 1 × 10^10^ bacterial cells. The activity for each strain is expressed as a percentage compared with the positive control *S. mutans* TW871, which has 100% binding activity to type I collagen (27). These experiments will be conducted by a researcher who is blinded to the clinical information.

### Assessment of Serum Antibody Titers Against Periodontal Pathogens

Serum samples will be collected during baseline evaluation to measure serum antibody titers against nine bacteria responsible for periodontal diseases by enzyme-linked immunosorbent assay, as previously reported (31). The nine bacteria are *Porphyromonas gingivalis* (*P. gingivalis*), *Aggregatibacter actinomycetemcomitans, Eikenella corrodens, Fusobacterium nucleatum, Prevotella nigrescens, Prevotella intermedia, Treponema denticola, Tannerella forsythia*, and *Campylobacter rectus*.

